## Abstract

**Aims:**

Coronary artery disease (CAD) remains a leading cause of morbidity and mortality worldwide, necessitating accurate diagnostic strategies and robust risk stratification. The FINESSE (Artificial Intelligence Stress Echo) study aims to develop and validate machine learning–based models to improve risk prediction in patients undergoing stress echocardiography (SE) for the assessment of inducible myocardial ischaemia, and to implement a structured AI-driven risk reclassification framework to support clinical decision-making.

**Methods and analysis:**

This is a retrospective observational study on prospectively recruited patients referred for SE with suspected CAD. Clinical, demographic, haemodynamic, and echocardiographic data will be extracted from institutional electronic health records and linked with longitudinal national datasets. The study employs a three-stage ML framework: (1) baseline risk estimation using QRISK3, (2) development and optimization of supervised ML models (including ensemble methods, support vector machines, and neural networks), and (3) longitudinal risk prediction using linked NHS England data (such as all-cause mortality and major adverse cardiovascular events, including cardiovascular death, non-fatal myocardial infarction, stroke, unplanned revascularization). Model performance will be evaluated using discrimination (AUC), calibration, and reclassification metrics, and will be externally validated using independent multicentre SE datasets.

**Conclusion:**

The FINESSE study will evaluate the incremental value of machine learning in SE by integrating multimodal data into a clinically actionable risk reclassification framework. This approach has the potential to improve personalized risk stratification, optimize diagnostic pathways, and support precision cardiovascular care.

**Protocol registration:**

Ethical approval has been obtained from the UK Health Research Authority and relevant research ethics committees, with appropriate data governance approvals for the use of routinely collected healthcare data. The FINESSE study is registered on ClinicalTrials.gov (Identifier: NCT07432620), ensuring transparency and public accessibility of the study protocol.

Key messages
**What is already known on this topic**—Stress echocardiography is a well-established clinical tool in the diagnosis and prognostication of patients with chest pain and effort breathlessness. Machine learning (ML) advances offer an opportunity to improve predictive modelling by integrating diverse clinical, imaging, and demographic datasets
**What this study adds**—The study seeks to enhance diagnostic accuracy and prognostication compared to traditional methods by integrating echocardiographic parameters with clinical and demographic data.
**How this study might affect research, practice or policy**—The proposed framework combining ML with clinical information along with SE parameters will be able to help doctors make better decisions about patient management while making healthcare more individualized.

## Introduction

The prevalence of coronary artery disease (CAD) continues to make it one of the top global health issues that cause both disease and death.^1,2^ Effective management relies on precise diagnosis and proper risk stratification. Stress echocardiography (SE) is a non-invasive bedside test used by healthcare professionals to diagnose CAD.^3–6^ It is particularly useful in assessing prognostic disease in patients with suspected CAD.^7,8^ Machine learning (ML) advances offer an opportunity to improve predictive modelling by integrating diverse clinical, imaging, and demographic datasets.^9^ ML algorithms find hidden patterns in data to create better patient risk groups and improve treatment results.^10^ This study aims to leverage ML techniques to develop and validate predictive models for outcomes in patients undergoing SE for the assessment of inducible myocardial ischaemia. The study seeks to enhance diagnostic accuracy and prognostication compared to traditional methods by integrating echocardiographic parameters with clinical and demographic data. Our research will be able to show that combining ML with clinical information along with SE parameters can help doctors make better decisions about patient management while making healthcare more individualized.

## Methods

### Study setting

This research project examines past data from a single hospital that performed SE on patients suspected of CAD. Our research team retrieved data from the institution's echocardiography and electronic health record (EHR) systems. A standardized data extraction, cleaning, and analysis protocol was implemented to ensure accuracy (*Figure 1*).

**Figure 1 qyag143-F1:**
[figure not shown]
Overview of the three-stage machine learning framework used in the FINESSE study.

### Eligibility criteria

#### Inclusion criteria

The study includes consecutive patients, 18 years or older, referred for a SE for inducible ischaemia detection for suspected CAD.

#### Exclusion criteria

Poor-quality echocardiographic description that preclude accurate interpretation or regional wall motion abnormalities (RWMAs) (thickening) at any stage of the SE protocol. Patients with known allergy to dobutamine or ultrasonic contrast enhancing agents (UCEAs) or who were referred for structural SE to assess severity of valvular abnormalities or left ventricular viability only were excluded. Patients who opted out data sharing were excluded from the study.

### Data collection

Data were collected using both SE reports and institutional EHR databases. Collected patient demographic information will include age, sex, race, height, weight, and body mass index. Cardiovascular risk factors such as; smoking habits, obesity status, family history of CAD, diabetes mellitus, essential hypertension, dyslipidaemia, prior CAD. Patients’ medical history at the time of the SE was also captured. Patients’ variables in support of calculating the QRISK-3 score^11^ was retrieved as complete as data permitted. (QRISK3 data extraction has been described in Supplement document). Extracted echocardiographic parameters include resting LV ejection fraction (from the WMS), and RWMA Wall Motion Score Index (WMSI) of the left ventricular 17 segments at each or the 4 stages of the SE protocol. (Detailed Dobutamine SE protocol and analysis is described in the Supplementary document.) To address inducible ischaemia the difference of the WMSI between low dose and peak stress of Dobutamine SE was calculated.^4,5^ Vital signs including systolic blood pressure (SBP), diastolic blood pressure (DBP), heart rate (HR) at rest and each stage of the SE protocol (low dose, peak stress, and recovery) were collected.

### Outcomes

All-cause death, hard endpoints: cardiovascular death, non-fatal myocardial infarction (MI) and composite outcomes will provide with different major cardiovascular events (MACEs), including stroke and unplanned revascularization, and hospital admission with progressive angina (MACE, 3-4-5) across four time periods: 1–3 years, 3–5 years, 5–10 years, and 10–20 years. The outcome data will be derived from NHS -England database with linking patients’ data such as NHS number and DOB and date of SE over 17 years after the indexed SE. (DARS-NIC-662451-S5L8J-v0.16).

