### Sample size calculation

The study aims to include approximately 2300 patients undergoing SE for the assessment of inducible myocardial ischaemia. The sample size was determined based on anticipated event rates, longitudinal outcome modelling requirements, and the complexity of the proposed ML framework.

Previous SE studies and cardiovascular outcome registries suggest that MACE are expected to occur at sufficient frequency within long-term follow-up to support robust prognostic modelling.^12^ The projected cohort size is anticipated to provide an adequate number of outcome events to satisfy event-per-variable requirements for both conventional statistical analyses and ML-based predictive modelling, while reducing the risk of model overfitting. The proposed sample size is also considered sufficient to support internal cross-validation, subgroup analyses, calibration assessment, and the evaluation of multiple supervised ML approaches, including ensemble methods, support vector machines (SVMs), and neural networks. In addition, linkage with longitudinal NHS outcome datasets over extended follow-up periods is expected to strengthen survival modelling and time-to-event prediction analyses.

External validation using independent multicentre SE cohorts is planned to further assess model generalisability and robustness across different clinical settings.

*
Table 1
* shows the characteristics of the patient population.

**Table 1 qyag143-T1:** Population characteristics

Variable	Total	Positive SE	Negative SE	*P*-value
Anthropometric variables				
*N*	2263	371 (16%)	1892 (84%)	—
Age (years)	63 (55–72)	64 (57–72)	63 (54–72)	0.031
Male Sex	1201 (53%)	243 (65%)	958 (51%)	<0.0001
Race				
Caucasian	2048 (91%)	330 (89%)	1718 (91%)	0.42
Asian	152 (7%)	27 (7%)	125 (7%)	0.85
Black	39 (2%)	8 (2%)	31 (2%)	0.71
Other	24 (1%)	6 (2%)	18 (1%)	0.31
Height (cm)	167 (160–175)	168 (160–176)	167 (160–175)	0.285
Weight (kg)	80 (68–95)	82 (70–98)	79 (67–94)	0.009
BMI (kg/m^2^)	28.7 (24.8–33.5)	29.0 (25.1–33.9)	28.6 (24.7–33.4)	0.198
BSA (m^2^)	1.90 (1.75–2.08)	1.93 (1.78–2.11)	1.89 (1.74–2.07)	0.012
Cardiovascular risk factors factors				
Hypertension	1371 (61%)	240 (65%)	1131 (60%)	0.072
Dyslipidaemia	1345 (59%)	238 (64%)	1107 (59%)	0.031
Current Smoker	218 (10%)	44 (12%)	174 (9%)	0.092
Former Smoker	648 (29%)	114 (31%)	534 (28%)	0.285
Diabetes Mellitus	671 (30%)	127 (34%)	544 (29%)	0.036
Obesity (BMI ≥30)	232 (10%)	30 (8%)	202 (11%)	0.142

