### Stage 1: clinical risk modelling and baseline assessment

#### QRISK3 risk estimation

QRISK3 is a validated clinical risk prediction model designed to estimate the 10-year risk of cardiovascular disease (CVD) using demographic and clinical variables.^11^ In this study, QRISK3 is used as a benchmark model against which ML-based approaches are evaluated.

Relevant patient characteristics and CAD risk factors were extracted from the local Hospital dataset and processed using the QRISK3 framework. The resulting risk estimates provide a clinically interpretable baseline for comparison with ML predictions (details of data extraction is provided in the Supplement).

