### Stage 3: model evaluation, longitudinal risk prediction using NHS England (aka digital) data

In the final stage, the local Hospital dataset was linked with NHS England longitudinal records, which include confirmed cardiovascular events. The performance of ML score to predict clinical events will be evaluated against base models of QRISK3, and SE ischaemia positivity. The forecasting power of future cardiovascular events over 5-year and 10-year will be assessed.

This longitudinal modelling framework enables dynamic risk prediction and supports early identification of individuals at elevated risk of adverse cardiovascular outcomes. We will be inviting external sites for validation and testing the robustness and scalability of the developed predictive algorithm in all spectra of SE modalities.

Internal validation once completed external validation is performed using independent multicentre cohorts, including EVAREST and Stress Echo 2030 to assess generalisability of the model. Model discrimination will be assessed using the area under the receiver operating characteristic curve (AUC) with 95% confidence intervals (CIs). Calibration will be evaluated using calibration-in-the-large, calibration slope, observed-to-expected event ratios, calibration plots, and the Brier score. Where systematic miscalibration is identified, model recalibration using intercept and slope adjustment will be undertaken prior to assessing clinical utility by. using risk reclassification analyses, including the net reclassification improvement (NRI).

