### Statistical methods

Participant demographics and characteristics are summarized with descriptive statistics. Categorical variables are expressed as median (interquartile range), and continuous variables are expressed as mean (standard deviation). Internal model validation will be performed with 5-fold cross-validation. Cox-regression model was fitted to estimate the hazard rates, hazard ratios (HR) and the 95% CIs. Survival probabilities from any event for the first time since SE will be evaluated using Kaplan–Meier curves. Performance evaluation for the model will include measurements of Accuracy alongside Sensitivity and Specificity, using receiver Operating Characteristic (ROC) analysis with c-statistics, together with calibration plots and risk reclassification. The study will perform comparative assessments between ML models and the QRISK3 calculator to evaluate their incremental predictive value. Statistical analyses will be performed using Stata 18.0 (StataCorp LP, College Station, TX) and the R environment (R 4.5.1, The R Foundation for Statistical Computing, http://www.R-project.org) using R studio (version 2024.12.1). All tests were two-sided and α was set at 0.05, unless specified otherwise.

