**Figure 2 qyag143-F2:**
[figure not shown]
FINESSE—machine learning model development workflow.

Baseline risk for each patient will be defined using conventional clinical assessment and QRISK3 derived estimates, as previously described. FINESSE AI will then generate an updated, individualized probability of the outcome of interest at a specified time horizon by integrating echocardiographic parameters, haemodynamic response variables, clinical characteristics, and longitudinal data. The integrated risk estimate will be defined as:

$$R_{F}(i,t)=f(R_{0}(i,t),X_{e}(i),X_{h}(i),X_{c}(i),X_{l}(i))$$

where $R_{0}(i,t)$ represents the baseline risk estimate and the additional inputs correspond to echocardiographic, haemodynamic, clinical, and longitudinal variables, respectively.

To facilitate clinical interpretation, continuous risk estimates will be mapped to predefined categories using a threshold-based classification function. These thresholds will be prespecified and subsequently evaluated against observed event rates within the study cohort to ensure appropriate calibration defined as low risk–intermediate risk–high risk.

Risk reclassification will be defined as a change in category between baseline and FINESSE-derived estimates, expressed as the difference between the categorical assignments derived from $R_{F}(i,\;t)$ and $R_{0}(i,\;t)$. Reclassification will therefore reflect either upward or downward movement across predefined risk strata. To minimize clinically insignificant shifts, reclassification will only be considered when the absolute change in predicted risk exceeds a predefined threshold, anticipated to be in the range of 3–5 percentage points. The predefined 3–5% risk reclassification threshold was selected because it represents the range within which relatively small improvements in estimated cardiovascular risk may influence guideline-directed management decisions, including initiation or intensification of lipid-lowering therapy, additional diagnostic testing, or referral for invasive coronary angiography. Similar thresholds have been adopted in previous cardiovascular risk prediction studies evaluating improvements in discrimination and clinical utility through net reclassification analyses. The threshold was therefore chosen to maximize clinical relevance rather than statistical optimization alone.

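### The outcome windows leave out the first year after stress echo, so they do not match the 5- and 10-year horizons; the last window also ends later than the stated follow-up

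*Protocol article*

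**What the plan says.** Five places in the protocol article fix a time origin or a horizon.

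- **Outcomes** lists death, cardiovascular death, non-fatal MI and several MACE composites "across four time periods: 1–3 years, 3–5 years, 5–10 years, and 10–20 years". The next sentence describes linkage to national records by patient identifiers and "date of SE over 17 years after the indexed SE".
- **QRISK3 risk estimation** makes QRISK3 the benchmark and describes it as a tool to "estimate the 10-year risk of cardiovascular disease (CVD) using demographic and clinical variables".
- **Stage 3** states: "The forecasting power of future cardiovascular events over 5-year and 10-year will be assessed".
- **Statistical methods** states: "Survival probabilities from any event for the first time since SE will be evaluated using Kaplan–Meier curves". Cox regression is planned alongside.
- **FINESSE AI–based risk reclassification framework** updates the baseline risk to an "individualized probability of the outcome of interest at a specified time horizon". The baseline and updated risks carry the same time index t, but t is given no value.

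No section describes the missing first year as a landmark or blanking period.

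**The concern.** The windows and the promised predictions do not describe the same quantity. A 5- or 10-year risk from the SE includes events on every day from the test onward; the windows begin counting a year later. Outcomes is the only section that defines the endpoints, so an analyst preparing the Stage 2 data would look there first.

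Stage 2 needs a yes/no label over a defined period. It plans random forest, gradient boosting, support vector machines and neural networks. Data preprocessing adds a split stratified on events and a correction for class imbalance, and performance is reported as accuracy, sensitivity and specificity. One analyst could label from the windows and another from the Stage 3 horizons. They would obtain different event counts, and so different AUC, observed-to-expected ratios and NRI. With window labels, the observed outcome would omit year 1 while the QRISK3 prediction covers ten full years.

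Two smaller defects sit in the same sentence. An event at exactly 3, 5 or 10 years belongs to two windows, and the last window ends at 20 years, beyond the only follow-up figure given.

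**Working it through.** The article states no event rate, effect size or formula, so there is no figure of its own to reproduce. The main check is interval arithmetic on the stated windows; the event shares are an illustration.

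**1. Coverage of the promised horizons**

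- To 5 years: (3 − 1) + (5 − 3) = 4 of 5 years, or 80%.
- To 10 years: 4 + (10 − 5) = 9 of 10 years, or 90%.
- In both cases the missing part is year 0–1. No sum of the stated windows gives a 0–5 or 0–10 year risk.

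**2. The last window against the stated linkage**

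- If follow-up spans 17 years: (17 − 10)/(20 − 10) = 7 of 10 years can be observed, and nobody can be followed from year 17 to year 20.
- If the phrase means more than 17 years, the shortfall is smaller or absent, but the article still states nothing that reaches 20.
- Under either reading, the 5- and 10-year horizons are unaffected.

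**3. Share of events in the missing year**

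Assumption, not from the article: a constant hazard h of 1% to 5% per year, with no competing risks. Then F(t) = 1 − exp(−ht), and the share of t-year events missed is F(1)/F(t). Counts use the 2263 patients in Table 1.

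Worked case, h = 2%: F(1) = 1 − exp(−0.02) = 0.0198 and F(5) = 1 − exp(−0.10) = 0.0952. The share is 0.0198/0.0952 = 20.8%, and 2263 × 0.0198 ≈ 45 patients.

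| h per year | 5-year risk from SE | sum of windows to year 5 | share missed | 10-year risk from SE | sum of windows to year 10 | share missed | patients missed |
|---|---|---|---|---|---|---|---|
| 1% | 4.9% | 3.9% | 20.4% | 9.5% | 8.5% | 10.5% | 23 |
| 2% | 9.5% | 7.5% | 20.8% | 18.1% | 16.2% | 10.9% | 45 |
| 3% | 13.9% | 11.0% | 21.2% | 25.9% | 23.0% | 11.4% | 67 |
| 5% | 22.1% | 17.2% | 22.0% | 39.3% | 34.5% | 12.4% | 110 |

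Sensitivity: if the first-year hazard were twice the later one, the share is (1 − exp(−2h))/(1 − exp(−h(t + 1))). Over the same range of h this gives 34.0–36.7% of 5-year events and 19.0–22.5% of 10-year events. The article does not say whether early risk is higher.

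**4. Scale against the reclassification rule**

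The absolute risk left out equals F(1): 1.0 to 4.9 percentage points across h = 1–5%, and 2.0 points at 2%. The framework counts a reclassification only when predicted risk changes by more than a threshold expected to lie at 3–5 points. A difference in horizon alone could therefore be of similar size to the change being judged.

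**5. After correction**

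With year 0–1 included, coverage is 5 of 5 and 10 of 10 years.

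**The case against.** The best defence is that the 5- and 10-year risks are provided for elsewhere. Statistical methods plans first-event survival from the SE, which includes year 1. The linkage carries the SE date, the model list includes Cox and random survival forests, and Stage 3 names its horizons separately. Nothing says that first-year events are discarded, or that the windows are the labels for the performance metrics; they may be reporting periods only. A partly observed last interval is ordinary right-censoring. Exact interval coding is commonly left to an analysis plan.

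Much of this stands, and it rules out several stronger readings that a reader might infer:

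- *That the study cannot deliver 5- and 10-year risks.* The planned survival analysis can; only the windows, taken alone, cannot.
- *That the 20-year bound undermines those risks.* It touches only the last window, and its force depends on how the 17-year phrase is read.
- *That the QRISK3 comparison is invalid.* It would be mismatched in horizon only if the windows supply the labels, which the article does not say.
- *That year 1 is when the test predicts best.* The article gives no support for this, and the point does not need it.
- *That each later window is restricted to patients event-free at its start.* No such condition is stated.

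The defence does not explain why the sole outcome definition begins at year 1, nor does it say which definition supplies the yes/no labels for the classifiers. That is a conflict between stated passages, not a detail left to a later document.

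**Conclusion.** The point holds as an inconsistency that should be reconciled before the models are trained and scored. The outcome windows omit the first year without a reason, overlap at three boundaries and end beyond the follow-up the article states. They do not match the Stage 3 horizons, the QRISK3 benchmark or the since-SE origin of the survival analysis.

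The coverage figures (4 of 5 and 9 of 10 years) need no assumption. The loss of about 20–22% of 5-year and 10–12% of 10-year events rests on two: that binary outcomes are labelled from the windows, and that the hazard is constant at 1–5% per year. If labels are instead taken cumulatively from the SE date, no first-year events are lost and what remains is a wording conflict.

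**What to change.** Define the outcomes used for model training, calibration and reclassification as cumulative from the SE date, with year 0–1 included and 0–5 and 0–10 years as the main horizons, in line with Stage 3. State which horizon applies to each metric, including the value of t in the reclassification formula. End the longest horizon at the follow-up actually available, say what the 17-year phrase means, and handle censoring. If risks by period are still wanted, keep them as secondary landmark analyses in patients event-free at the landmark, with non-overlapping boundaries. If leaving out year 1 is deliberate, give the reason and align the other sections with it.

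The cost is protocol and analysis-plan wording and recoding of linked event dates. No new data are needed. The article defers all model performance results to a later manuscript, so the definition can still be corrected before they are reported.
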